##### Primary and secondary outcome measures

Primary outcome measures: HAMD-17 (33). The severity of depressive symptoms will be assessed using the total score of HAMD-17. The higher the score, the more severe the depressive symptoms.

Secondary outcome measures: Snaith–Hamilton Pleasure Scale (SHAPS) (34). The scale includes four aspects of interest/entertainment, social interaction, sensory experience, and food/drink, and has a total score of 14 to 56. It has good validity and reliability to evaluate the hedonic experience of adult outpatients with MDD (35).

The changes in depression and anhedonia symptoms will be assessed using HAMD-17 and SHAPS before and after the NF intervention, respectively. Follow-up assessments of depression (HAMD) and anhedonia (SHAPS) symptoms will be conducted at 3 and 6 months after the intervention.

##### Behavioral task

The reward learning task (two-stage Markov decision task) (30) will be adopted. All participants will practice an 8-min Markov decision task outside of the scanner room before formal NF training, for which instructions will be provided to the participants. After practice, the participants will rest for 5 min before completing the formal NF training. The practice and formal tasks will be presented using MATLAB 2019a (https://www.mathworks.com) and Psychtoolbox 3.0 (http://psychtoolbox.org).

The task will be divided into two stages. In stage 1, participants choose one of two stimuli (red) (stage 1, left panel), which leads to the second stimulus (green) in 70% of the cases and to the third stimulus (blue) (stage 2) in 30% of the cases. The other stimulus (stage 1, right panel) leads to the second stimulus (green) in 30% of the cases and to the third stimulus (blue) in 70% of the cases. The six stimuli at the two stages will be selected from the alphabets that are unfamiliar to the participants to encourage progressive learning. The possibility that the stimulus of stage 1 changes to the second stage through the key press of participants is called the transition probability (common transition 70% vs. rare transition 30%). The selection of experimental stimuli in stage 2 may result in either a reward or no reward. To motivate participants to continue learning, the reward will follow a slowly drifting Gaussian random walk with probability changes ranging from 0.25 to 0.75 (Figure 3).

**Figure 3 F3:**
[figure not shown]
Schematic diagram of the Markov reward decision task adapted from Daw et al. (30).

Participants will be encouraged to make options to receive as many rewards as possible and will be informed prior to practice and formal experiments that all rewards will be paid off at the end of the experiment. The task flow is as follows (Figure 4).

**Figure 4 F4:**
[figure not shown]
Flowchart of the Markov reward decision task, adapted from Daw et al. (30).

#### Real-time fMRI neurofeedback of individual goal-directed system in anhedonic depression

The anhedonic depressed participants (*n* = 40) will be randomized into the neurofeedback (NF) group (*n* = 20) and the yoke control (YC) group (*n* = 20). We used blocked randomization to form the allocation list (1:1 ratio) for the two comparison groups (NF and YC), by using a computer random number generator to select random permuted blocks (size = 10). The NF group will receive rt-fMRI neurofeedback intervention, with ~60 min per session, once per week for a total of four sessions. Participants in the YC group who are paired with one specific participant from the NF group will receive feedback signals from that participant during the same run. Thus, for the YC group, the sham rt-fMRI signals will not be corresponding to the participant's brain activity. The healthy control (HC) group (*n* = 20) will receive no intervention.

##### Sample size

The sample size is determined based on a heuristic justification (36) according to median recruits (*n* = 18) of fMRI neurofeedback (37). Moreover, given that this is a feasibility study with constraints on limited resources, a power calculation is not necessary according to the reporting and experimental design consensus in the NF field (38).

##### Real-time magnetic resonance imaging

MR images will be collected using 3.0T Siemens (Trio, Erlangen, Germany) with a 32-channel head coil. T1-weighted structural images will be collected from the whole brain with the magnetization-prepared rapid gradient echo (MPRAGE) sequence for anatomical localization of functional images. FOV = 256 × 256 mm, 176 sagittal slices, layer thickness = 1.0 mm, resolution = 1.0 mm^2^, TR/TE = 1900/2.52 ms, and flip angle = 9°. Echo-planar imaging (EPI) T2^*^-weighted functional images will be collected across the whole brain using a gradient echo planar imaging (EPI) sequence, FOV = 192 × 192 mm, matrix size = 64 × 64, and spatial resolution = 3 × 3 × 3 mm^3^, flip angle = 90°, and TR/TE = 2000/30 ms. To reduce the head motion, a strip of medical tape will be attached horizontally over the forehead of the participant and be spread to both sides of the head coil so that the participant could feel the head motion subjectively to prevent it from exceeding the range of head motion (39).

Real-time functional imaging will be achieved by using a customized function during MR image reconstruction, with TurboExport (Brain Innovation, Maastricht, The Netherlands) to convert input pixel data for each volume into images. Each image generated will be preprocessed in real time using the Turbo-BrainVoyager (Brain Innovation, Maastricht, The Netherlands). Preprocessing includes motion correction (by realigning each image to the first image of the session) and spatial smoothing (Gaussian kernel of half-height and 5 mm in full width). The computer presenting the task will communicate with Turbo-BrainVoyager via Transmission Control Protocol (TCP) to acquire preprocessed real-time data to be coregistered to the localizer anatomical image (first session) and generate feedback displays to the participants.

##### Network-based rt-fMRI NF intervention

The network-based rt-fMRI NF intervention of each session will be divided into 6 runs (5 NF runs and 1 transfer run), at 10 min/run. Subjects will be asked to raise or lower the height of a progress bar on the screen through cognitive effort. The height of the bar will depend on the signal intensity of regions of interest (ROIs) in the CEN and SN measured on each trial. Participants will be asked to regulate their brain signals through internal thought without specific instructions, with the feedback signaling the balance between the average signal intensities of the CEN and SN. They will know neither the source nor the calculation of the feedback signal. Before each session, participants will be explicitly instructed to try to avoid movement, including facial expressions, limb movements, and irregular breathing patterns.

During the scan, anatomical images will be recorded first (~5 min) and preprocessed immediately after image reconstruction based on a separate computer using BrainVoyager. After that, the results will be transmitted to Turbo-BrainVoyager to obtain real-time functional data aligned to the target ROIs of neurofeedback. Each run will start with a rest phase, during which the baseline and change in the feedback signal will be calculated. The feedback will be based on the differential signal between the mean values of all the voxels in the individualized ROIs in the CEN and SN. The baseline for this difference signal will be defined as the median difference between the initial resting signal of the SN and the CEN ROIs, and the lower and upper limits will be set to be two standard deviations from this baseline. The upper and lower limits will be updated to the average of the five lowest/highest median differences of this run before each block (29). The regulatory success targets the larger differential signal between CEN and SN. The transfer run will test the generalization of NF training without feedback signals during which the participants will be required to regulate their brain signals in the same way as the NF training run (40).

After each run, the participants will appraise their control over the progressive bar height (0–10 points) and their cognitive difficulties (0–10 points) with handles. Between runs, the participants will be allowed to rest for 5 min without significant head movement. After the NF intervention outside the scanner, the participants will write down the strategies they used to regulate their brain signals (e.g., through internal thought) and evaluate the effectiveness of strategies (0–10 points). To evaluate the demand characteristics, they will also indicate which group (NF or YC) they believe they belong to.

### Statistical analysis

#### Behavioral data

##### Statistical analysis

IBM SPSS Statistics 22 (https://www.ibm.com/spss) will be used. The 2 (groups: high anhedonia group and healthy control group) × 2 (transition conditions: common transition and rare transition) × 2 (reward feedback: reward and non-reward) factor mixed design will be conducted. The general linear mixed model (GLMM) will be used to investigate the main effects and interactions of the group, transition condition, and reward feedback on choice behavior. The interactions of transition conditions and reward feedback will represent the effect of the goal-directed system on the choice behavior (goal-directed RL), and the main effect of reward feedback will represent the effect of the habitual system on the choice behavior (habitual RL). The three-way interaction of the group, transition condition, and reward feedback will be examined to test for group differences in goal-directed RL. The two-way interaction of group and reward feedback will be examined to test for group differences in habitual RL.

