### Participants

The study was approved by the ethical review committee at the Army Medical University (AMU, PRC) and conformed to the Declaration of Helsinki. The study has been submitted to the Chinese Clinical Trials Registry (ChiCTR, https://www.chictr.org.cn/). The trial identifier will be made available upon approval of the registration. After signing the informed consent form, the clinical data and general information of all participants will be collected, including age, gender, duration of illness, years of education, and medication history. The clinical diagnosis and symptom assessment will be completed by psychiatrists according to DSM-5 combined with a Mini-international Neuropsychiatric Interview (MINI). We will use the Hamilton Depression Scale-17 (HAMD-17) and the Montgomery–Åsberg Depression Rating Scale (MADRS) to assess anhedonia symptoms. Participant selection and recruitment processes were not conducted prior to the submission of the study.

(1) High anhedonic depression group. Inclusion criteria: ① diagnosed with major depression, with at least one core symptom (loss of pleasure or interest in all or nearly all activities) (MADRS item 8 ≥ 4) or non-reactive mood (items 1 or 2 ≥5, ② at least three following symptoms during the most severe phase of this depressive episode, including (a) significant psychomotor disturbance (HAMD items 8 or 9 ll1); (b) appetite/weight loss (HAMD items 12 or 16 = 2); (c) late insomnia (waking at least 2h earlier than usual) (HAMD item 6 ≥ 1); and (d) guilt (HAMD ≥ 1) (32); ③right-handedness. Exclusion criteria: ① comorbid with other mental disorders or drug or alcohol dependence; ② has received any previous antidepressant or antipsychotic medication (including benzodiazepines and other sedatives and hypnotics); ③ with severe physical diseases such as heart, liver, or kidney impairment, endocrine disorders, or infectious diseases; ④ substance dependence or abuse; ⑤ vision impairments; ⑥ pregnant or breastfeeding women; ⑦ MRI contraindications; and ⑧ currently receiving any emotional ability training.

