##### Computational modeling

MATLAB 2019a (https://www.mathworks.com/) and the Reinforcement Learning algorithm will be used to model the behavioral data and estimate the learning rate α, inverse temperature parameter β, repetition parameter p, and model-based learning weight ω of individual subjects.

① value estimates. The state-action values for the first and second stages of each trial are determined by the weighted sum of the model-based action value Q_MB_ and the model-free action value Q_MF._ The weighted sum is expressed as follows.

(1)
$$\begin{array}{l} Q_{net}\left(S_{A},a_{j}\right)=\omega Q_{MB}\left(S_{A},a_{j}\right)+{\left(1-\omega \right)Q}_{MF}\left(S_{A},a_{j}\right) \end{array}$$

It is assumed that individual behavioral choice in the first stage is the weighted sum of goal-directed and habitual learning, with the weight of ω (0~1). If ω is close to 0, the choice mainly depends on habitual learning; if ω is close to 1, the choice mainly depends on goal-directed learning.

(a) Model-based state-action value:

(2)
$$\begin{array}{l} Q_{MB}(S_{A},a_{j})=P(S_{B}|S_{A},a_{j})\underset{a\in \{a_{A},a_{B}\}}{\max}Q_{MF}(S_{B},a)\\ \;+P(S_{C}|S_{A},a_{j})\underset{a\in \{a_{A},a_{B}\}}{\max}Q_{MF}(S_{C},a) \end{array}$$

(b) Model-free state-action value:

(3)
$$\begin{array}{l} Q_{MF}\left(S_{i,t},a_{i,t}\right)=Q_{MF}\left(S_{i,t},a_{i,t}\right)+\alpha_{i}\delta_{i,t} \end{array}$$

For the first and second stages, learning rates α_1_ and α_2_, respectively, represent the extent to which the reward results are used for learning.

(c) Prediction error:

(4)
$$\begin{array}{l} \delta_{i,t}=r_{i,t}+Q_{MF}\left(S_{i+1,t},a_{i+1,t}\right)-Q_{MF}\left(S_{i,t},a_{i,t}\right) \end{array}$$

The action probabilities of the first and second stages of each trial are regarded as a softmax function of the inverse temperature parameter β, the repetition parameter *rep*, and the indicator function *p* as follows.

(5)
$$\begin{array}{l} P(a_{i,t}=a|s_{i,t})=\frac{exp(\beta [Q_{net}(s_{i,t},a)+p\cdot rep(a)])}{\sum_{a^{\prime }}exp(\beta_{i}[Q_{net}(s_{i,t},a^{\prime })+p\cdot rep(a^{\prime })])} \end{array}$$

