The inverse temperature parameters β_1_ and β_2_ represent the randomness of the first- and second-stage choices. The repetition parameter p and the indicator function represent the reproducibility of the choice, that is, the tendency to choose the same choice as in the previous trial, regardless of the actual value of the choice. Additionally, *p* > 0 represents choices the same as the previous trial, and *p* < 0 represents choices different from the previous trial.

The parameters of each subject will be estimated using the R software and its Stan toolkit with the Markov Chain Monte Carlo (MCMC) estimation which has been previously described (4). The model evidence of the Akaike information criterion (AIC) and the Bayesian information criterion (BIC) will be calculated separately to estimate the model fit of reinforcement learning to the behavior.

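### The non-randomised patient–control test of goal-directed learning has an age range for controls only and no age term, and its model name leaves the link for a binary choice unclear.

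*Protocol article*

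**What the plan says.** **The test.** Under Behavioral data, Statistical analysis, the protocol article sets out a mixed design: "The 2 (groups: high anhedonia group and healthy control group) × 2 (transition conditions: common transition and rare transition"), with reward feedback as the third factor. The model is described as follows: "The general linear mixed model (GLMM) will be used to investigate the main effects and interactions of the group, transition condition, and reward feedback". The inferential target is then fixed: "The three-way interaction of the group, transition condition, and reward feedback will be examined to test for group differences in goal-directed RL". No covariate, response distribution or link is named.

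**The response.** Under Behavioral task: "In stage 1, participants choose one of two stimuli (red"). At trial level the stage-1 response is therefore binary. The transition split is "common transition 70% vs. rare transition 30"%.

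**The groups.** Under Participants, the patient list opens with "diagnosed with major depression, with at least one core symptom" and runs through three inclusion and eight exclusion items, none of which concerns age. The control list next to it limits age to 18–55. No matching is described. The same section says that age, gender and years of education are collected from every participant.

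**Where age is used.** The only analysis with an age covariate is the Bayesian ANCOVA of NF against YC, under Primary and secondary outcomes, which also adjusts for gender and duration of illness.

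**The choice model elsewhere.** Under Computational modeling: "The action probabilities of the first and second stages of each trial are regarded as a softmax function of the inverse temperature parameter β". That model gives repetition its own parameter, described as "the tendency to choose the same choice as in the previous trial, regardless of the actual value of the choice".

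**The concern.** There are two separate weaknesses in one test.

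1. **Age.** Patients and controls are not randomised against each other, so only the eligibility criteria, matching or the model can balance age. The criteria bound age in one group only, no matching is stated, and the model omits age. Adjustment is written for the comparison that randomisation already protects and not for the one that it does not. The Introduction itself links goal-directed deficits to the lifespan.

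2. **Model name.** The words describe a general linear mixed model, while the acronym usually stands for the generalized one. For a yes/no response the difference matters. On the probability scale, the size of a reward × transition effect depends on how often a group repeats its choice at all. Repetition is something the plan itself treats as distinct from goal-directed control.

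At stake is the behavioural part of the Abstract's first aim. A group difference in the interaction might reflect age or the measurement scale and not illness.

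**Working it through.** The article gives no alpha, power, effect size or age slope for this test, so there is no figure to reproduce. Two-sided 5% is assumed throughout.

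**Inputs from the document:** 40 patients (20 NF + 20 YC), 20 controls, 70/30 transitions, binary stage-1 choice.

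**A. Age bias, by hand**

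Bias = age slope × difference in mean age. Assume a slope of 0.1–0.2 SD per decade and a gap of 10 years:
- bias = 0.1 × 1 to 0.2 × 1 = 0.1–0.2 SD
- standard error of the group difference = √(1/40 + 1/20) = 0.274 SD
- bias/SE = 0.1/0.274 = 0.37 and 0.2/0.274 = 0.73
- rejection with no disease effect = Φ(−1.96 + 0.37) + Φ(−1.96 − 0.37) ≈ 6.5%, and likewise ≈ 11.3% at 0.73

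**B. Age bias, by simulation**

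Further assumptions: 200 trials, 50% reward, logit reward effect 0.3, logit reward × transition effect 0.4 with between-subject SD 0.25, random-intercept SD 0.6, equal baseline repetition. Each subject's interaction contrast is compared between groups by a Welch test; this approximates a random-slope model. There is no disease effect, patients are older, and there are 2,000 replicates per cell. Rejection on the logit scale:

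| Fall in logit effect per year | Gap 5 y | Gap 10 y | Gap 15 y |
|---|---|---|---|
| 0.004 | 5% | 7% | 10% |
| 0.008 | 8% | 14% | 27% |
| 0.012 | 10% | 25% | 51% |

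With no gap the rate is about 5%. The probability scale gives nearly the same values, so changing the link does not cure the age problem.

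**C. Why the link matters**

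Take logit(stay) = b0 + 0.3R + 0.4RT, with R and T coded ±1 and the same 0.4 in both groups. The interaction on the probability scale is the mean of p × RT over the four cells, in the order rewarded-common, rewarded-rare, unrewarded-common, unrewarded-rare:
- b0 = 0.5: (0.7685 − 0.5987 − 0.4502 + 0.6457)/4 = 0.091
- b0 = 1: (0.8455 − 0.7109 − 0.5744 + 0.7503)/4 = 0.078
- b0 = 2: (0.9370 − 0.8699 − 0.7858 + 0.8909)/4 = 0.043

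The logit effect is identical, yet it shrinks as repetition rises.

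False-positive rates under the assumptions in B, with no true group difference on the logit scale and 3,000 replicates. Rates are the stay probability at the baseline logit:

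| Stay rate, controls vs patients | Identity scale | Logit scale | Direction on identity scale |
|---|---|---|---|
| 73% vs 73% | 5.1% | 4.9% | none |
| 73% vs 62% | 9.7% | 5.4% | false excess |
| 73% vs 82% | 13.9% | 4.7% | false deficit |
| 62% vs 82% | 30.5% | 5.4% | false deficit |
| 73% vs 88% | 45.7% | 5.5% | false deficit |
| 62% vs 88% | 65.7% | 5.2% | false deficit |

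**The case against.** **On the model.** A reader might infer that the plan commits to a Gaussian linear model for a binary response. The text does not support that. It says mixed, uses the acronym GLMM, and states no link, so a naming slip is at least as likely. Link and random-effect structure are also details that an article may leave to a fuller document. This stands. What remains is that the printed name and the acronym disagree and the choice affects the key test.

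**On direction.** A reader might also infer that the test is set up to show a false deficit in patients. It is not. The scale artefact produces a deficit only if patients repeat more, and an excess if they repeat less. Age produces a deficit only if patients are older and goal-directed learning declines with age. The document gives no reason to expect a repetition gap, and no ages.

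**On size.** The simulated data were generated on the logit scale, which favours the logit analysis, and the larger inflation rates need large assumed gaps. The hand-calculated age bias is below one standard error. Both remarks are fair. Nor is a logit link a complete cure: in the article's Equation 5 the inverse temperature multiplies the values, so a group difference in choice randomness would alter a logit-scale interaction with ω unchanged.

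**On scope.** The stated Aims concern neurofeedback, and the model-based weight ω, estimated with repetition separated out, is what goes into follow-up and mediation. That limits the importance of the point. But no patient–control test of ω is stated, so the three-way interaction remains the named test.

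None of this answers the age asymmetry: a limit printed for one group and absent from the adjacent list is not explained by condensation.

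**Conclusion.** The age point holds on the text. Age is bounded for controls only, no matching is stated, and the non-randomised comparison is unadjusted. The resulting bias may run either way, and its size depends on who is recruited and on a slope that the document does not give. At 0.1–0.2 SD per decade and a 10-year gap it is 0.1–0.2 SD, or roughly 7–11% rejection instead of 5%. Across the simulated slopes and gaps of 5–15 years the range is about 5–51%. This is an exposure, not a demonstrated bias.

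The model point holds as an ambiguity. Only if an identity link were used, and only if repetition rates differ, would the test be inflated: about 10–14% for baseline gaps of 0.5 logit and about 30–46% for gaps of 1 logit under the stated assumptions. At equal repetition there is no inflation.

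The primary NF vs YC comparison of HAMD-17 is randomised, adjusts for age, and is untouched.

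**What to change.** 1. Reconcile the two eligibility lists so that patients and controls have the same age range, or match the groups on age.
2. Add age and gender, each with its interaction with reward × transition, to the patient–control model. A main effect of age alone would not protect the three-way interaction. Education is also recorded but is not shown to differ between the groups; with 20 controls, a short covariate list is preferable.
3. Correct the model name to a generalized linear mixed model with binomial distribution and logit link, and by-subject random effects (an intercept, and slopes for reward, transition and their product).

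The cost is one eligibility line and a few words of analysis text, possibly slightly fewer eligible patients, and a few degrees of freedom. The article states that recruitment had not begun at submission, so at that stage the changes could be made without affecting enrolled participants.

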#### Pre- and post-test

Before and after the neurofeedback intervention, the primary and secondary outcome measures of the depressive and anhedonic symptoms will be assessed in all subjects. The behavioral tasks will be repeated post-training to evaluate the NF training effect on goal-directed behavior. The follow-up assessments include the primary outcome of depression and secondary outcome of anhedonia, the goal-directed RL (model-based weighting parameter ω), and the CEN-SN functional connectivity (Pearson's correlation) based on prediction errors (PEs) (Figure 2).

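### The interaction used to test patient-control differences in goal-directed learning also moves with choice consistency and learning rate; a deficit claim should also require a lower ω

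*Protocol article*

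**What the plan says.** Under Behavioral data, Statistical analysis, a mixed model of choice has the factors group (high anhedonia versus healthy control), transition and reward. The section states how the terms will be read: "The interactions of transition conditions and reward feedback will represent the effect of the goal-directed system on the choice behavior", and then "The three-way interaction of the group, transition condition, and reward feedback will be examined to test for group differences in goal-directed RL". The group × reward term is read in the same way for habitual RL.

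Two other sections tie the same construct to a model parameter. Pre- and post-test lists "the goal-directed RL (model-based weighting parameter ω" among the follow-up measures. Computational modeling assumes that "individual behavioral choice in the first stage is the weighted sum of goal-directed and habitual learning", with weight ω, and adds that "if ω is close to 1, the choice mainly depends on goal-directed learning".

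The same section says that the action probabilities "are regarded as a softmax function of the inverse temperature parameter β" (Equation 5). It explains that the inverse temperatures "represent the randomness of the first- and second-stage choices". The plan will "estimate the learning rate α, inverse temperature parameter β, repetition parameter p, and model-based learning weight ω of individual subjects", so the quantities needed to separate ω from β are already to be produced. The article states uses for ω as a follow-up measure, an imaging covariate and a mediator. It states none as a patient-control contrast.

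**The concern.** One construct has two measures that are not interchangeable. ω is relative: it places choice between habitual and goal-directed learning. The interaction is absolute: it is the size of the goal-directed influence on observed choice, and it shrinks when choice becomes more random.

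The difference matters in this contrast because group is diagnosis. Randomisation does not balance choice consistency or learning rate between patients and controls. The Discussion names motivation and effort as possible confounders, but the yoked design that it offers as the remedy protects only NF versus YC; healthy controls receive no intervention. A significant three-way term could therefore be reported as impaired goal-directed learning when patients only chose less consistently or learned more slowly. A true ω deficit could also go unseen if patients were the more consistent responders.

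**Working it through.** The article gives no power, effect size or error rate for this test, so there is no figure of its own to reproduce.

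**Inputs from the article.** Transition probabilities 0.7/0.3 and reward probabilities drifting within 0.25-0.75 (Behavioral task); Equations 1-5 (Computational modeling); 40 patients and 20 healthy controls (section on real-time fMRI neurofeedback of the individual goal-directed system).

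**Assumptions.** Two-sided 0.05; 200 trials per person; control β = 5; ω = 0.5; α1 = α2 = 0.5; p = 0.15; between-person SD 0.15 for ω and 0.25 for log β; reward drift SD 0.025. Lower β in patients is a scenario that the article neither asserts nor rules out.

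**Analytic step.** From Equations 1 and 5, the first-stage log-odds are β1[ω·ΔQ_MB + (1−ω)·ΔQ_MF + p·Δrep]. By Equation 3, reward rather than no reward raises the chosen second-stage value by α2. By Equation 2, this moves ΔQ_MB by +(0.7−0.3)·α2 after a common transition and by −(0.7−0.3)·α2 after a rare one, provided that action is the better one in its state. Hence

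transition × reward contrast ≈ 0.8·β1·ω·α2.

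- β 5, ω 0.5, α 0.5: 0.8 × 5 × 0.5 × 0.5 = 1.0 (simulated 0.95).
- β 2.5, same ω and α: 0.8 × 2.5 × 0.5 × 0.5 = 0.5 (simulated 0.43). The contrast halves with ω unchanged.
- β 5, ω 0.5, α 0.35: 0.8 × 5 × 0.5 × 0.35 = 0.7. A lower learning rate has the same kind of effect.

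**Simulation.** Each person's transition × reward contrast on stay/switch was compared between groups by a Welch test, as a stand-in for the mixed-model term, with 1,000 replicates per setting. The article names no link function, so both scales are shown. Entries are false deficits (significant, patients lower) with equal ω and control β = 5.

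| Patient β | Logit, eligibility trace 0.6 | Logit, no trace | Raw probability, trace 0.6 |
|---|---|---|---|
| 5 | 2.7% (any rejection 4.3%) | – | 3.0% |
| 4 | 13.3% | 14.5% | 6.2% |
| 3.5 | 25.4% | 27.4% | 10.0% |
| 2.5 | 57.3% | 59.5% | 29.0% |

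Sensitivity, logit scale with trace 0.6:

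- ω from 0.3 to 0.7: 13-41% at patient β 3.5 and 29-85% at 2.5.
- 100 to 300 trials at patient β 3.5: 15-29%.
- Learning rate alone lower (0.35 versus 0.5): 17%.

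A second simulation used p = 0.1 and SDs of 0.3 on log β and 0.6 on logit ω. For β 2.5 versus 5 it gave total rejection of 58-64% (logit) and 38-47% (raw).

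**Masking.** With ω 0.4 and β 5 in controls and ω 0.8 and β 2.5 in patients, β·ω is 2.0 in both groups. The logit test rejects 7.3% of the time, so a doubled ω is mostly missed. A true deficit (ω 0.4 versus 0.6, equal β) is detected 27% of the time on the logit scale, about the same as the false rate for β 3.5 versus 5. In the second simulation, with ω 0.35 in patients and 0.55 in controls, power fell from 23-24% with equal β to 4-6% with β 5 in patients and 3.5 in controls.

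**Comparing fitted ω instead** (400 replicates, true ω 0.5 in both groups, control β 5):

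| Patient β | ω: false deficit | ω: any rejection | Logit interaction: false deficit |
|---|---|---|---|
| 3.5 | 2.5% | 6.2% | 23.2% |
| 2.5 | 1.0% | 8.5% | 56.5% |

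The group difference appears where it belongs: fitted β1 differs significantly in 92% and 100% of replicates.

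**The case against.** The strongest reply is that the behavioral section defines its own quantity. It reads the interaction as the effect of the goal-directed system on choice, and in Equations 1 and 5 the coefficient on Q_MB is β·ω. A lower β·ω is then a true reduction in absolute influence, and calling it false presupposes the relative definition. This stands in part: the interaction is a legitimate model-free index and need not be dropped. But the article also identifies goal-directed RL with ω, and its reading of the three-way term does not separate the two.

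The group × reward term is a partial safeguard, since noisier choice shrinks it too: it was rejected 30% of the time at patient β 3.5 and 76% at 2.5. A fall in both indices would hint at a non-specific effect, but not reliably.

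A reader might infer more than the documents support:

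- That the test will report a deficit far above 5%. The article gives no β, α, trial count or variance, and no patient-control gap in β. For a 20% gap on the raw-probability scale the rate is only about 6%.
- That the trial's rationale or main result depends on this test. The Abstract speaks of exploring CEN/SN deficits, the Aim section contains no patient-control comparison, and the neurofeedback rationale is drawn from earlier work.
- That no ω comparison is planned anywhere. The article is condensed and refers to a preregistration and a checklist that are not shown. The point rests on the reading that the article does state.

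**Conclusion.** The point holds as a limit on interpretation. A smaller three-way interaction in patients shows a smaller product of choice consistency, ω and learning rate; it does not by itself show a lower ω. How often this would mislead depends on patient-control gaps that the article does not give. Under the stated assumptions it runs from near nominal with equal β to 29% (raw probability) or 57-60% (logit) when patient β is half the control value. The Welch test approximates the mixed model, so these rates are indicative. Only the patient-control mechanism analysis is affected; the Bayesian ANCOVA of NF versus YC on HAMD-17 is not. This is an inexpensive improvement worth making.

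**What to change.** In Behavioral data, Statistical analysis, add a patient-control comparison of ω from the Stan model already planned under Computational modeling. Include group terms for β1, β2, α1, α2 and p, and report them beside ω. Keep the three-way and group × reward interactions as the model-free analysis of absolute influence on choice. State that a specific goal-directed deficit will be concluded only if ω itself is lower in patients.

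The cost is a few sentences and group-level terms in a model that will be fitted anyway; no new data are needed. There is a small downside. The ω comparison relies on the learning model being correctly specified, and its total rejection reached 8.5% in one check, although 7.5 points of that (8.5 − 1.0) were in the direction of higher ω in patients. Its power with 40 versus 20 was not calculated, so a non-significant ω difference should not be read as evidence of equal ω.
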